#### Secondary outcome measures

The following are the secondary outcome measures:
Quality of life using the SF-36 Questionnaire: The SF-36 is a short-form, multipurpose health survey with only 36 questions. The instrument contains eight subscales (physical function, physical role, body pain, general health, vitality, social function, emotional role and mental health) and two summary scores: physical and mental health. Scores range from 0 to 100% and indicate the self-perceived health-related quality of life [49, 50].Tampa Scale for Kinesiophobia (TSK): This is a 17-item questionnaire that measures fear of movement and (re) injury. Patients rate their beliefs about their kinesiophobia on a 4-point scale ranging from strongly disagree to strongly agree [51, 52].Pittsburgh Sleep Quality Index (PSQI): This is a 10-item questionnaire with a total of 19 questions related to sleep habits in the previous month. The questions are divided into 7 areas, each with a score of between 0 and 3 points. The overall score ranges from 0 (no difficulty sleeping) to 21 points (severe difficulty sleeping) [53].Hospital Anxiety and Depression Scale (HADS): This scale consists of 14 items related to emotional distress (anxiety, depression) in populations suffering from a physical illness. It consists of two subscales (HADA: anxiety and HADD: depression) with seven items each that score from 0 (normal) to 3 (abnormal) [54, 55].McQuade Test: This test evaluates the isometric resistance of the flexor muscles of the trunk. The patient is placed supine and asked to flex the head and shoulders until the scapula is lifted off the table. The number of seconds they hold that position is recorded [56].Anterior trunk flexion. Standing, with legs straight, the patient is asked to bend forward and attempt to touch the ground. They are told to stop when pain or limitation of movement appear. The distance, in centimetres, between the fingers and the ground is measured [57].Spinal Mouse®: This is a safe, practical and easy-to-use instrument to measure the curvature of the spine in the frontal and sagittal planes and to assess the segmental mobility of the lumbar region [58].Pressure algometry (Wagner FPI 10 Algometer) in MTrPs: The algometer consists of a rubber tip and a dial that measures the pressure applied to the MTrP in increments of 0.5 kg. The pressure pain threshold will be assessed following the illustrations published by Travell and Simons [14].

### Sample size

The sample size was calculated according to the specifications established by Willian [59]. The calculations were based on the detection of differences of 2.5 points in the RMDQ (minimum detectable difference between means for a variance of 10 points in patients with chronic low back pain), assuming a standard deviation of 2.5 points, a 2-tailed test, an alpha (*α*) of 0.05 and a target power (beta) of 85%.

The following specifications will be considered: *α* = 0.05, statistical power of 85% and loss to follow-up of 15%. The sample size calculation yielded a total of 92 participants to be randomized to two intervention groups.

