**Methods:**

This is a controlled, randomized, two-arm, double-blind study. A total of 92 patients with chronic low back pain (time to onset ≥ 3 months, Roland Morris Disability Questionnaire score ≥ 4) will be recruited from the University of Almería. Participants will be divided into two study groups (*n* = 40) to receive treatment of low back pain with electrical dry needling and conventional physiotherapy (ischaemic compression, analytic stretching and postural education training dossier). A total of 6 sessions will be administered once a week for 6 weeks. Pain intensity, disability, fear of movement, quality of life, quality of sleep, anxiety and depression, pressure pain threshold, abdominal strength and lumbar mobility will be recorded at 6 weeks (post-immediate) and 2 months after the end of treatment.

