### Randomization and blinding

Participants will be randomized to two groups using a computer-generated (Epidat 4.2) table of random numbers generated. After randomization, participants will be assigned to either the experimental electrical dry needling group or the conventional physiotherapy control group in a ratio of 1:1. Randomization will be performed by the principal investigator.

There will be 46 participants in each group. The randomly generated group allocations will be placed in sealed opaque envelopes before being delivered to the participants and stored in locked cabinets.

The outcome assessor and study statistician will be blinded to the entire process. The outcome assessor will make no attempt to guess the participant’s treatment group. The computer-generated outcome measures transmitted to the statistician will not contain any information that identifies the patient’s group.

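### The total of 92 does not follow from the stated sample-size inputs, which give 44 to 46 (SD 2.5) or 70 to 72 (variance 10), and the abstract's group size disagrees with the body

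*Protocol article*

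**What the plan says.** The Sample size section of the protocol article bases the calculation on the "detection of differences of 2.5 points in the RMDQ". It describes this in parentheses as the "minimum detectable difference between means for a variance of 10 points in patients with chronic low back pain", and the sentence then continues "assuming a standard deviation of 2.5 points, a 2-tailed test". Alpha is 0.05, power is 85% and loss to follow-up is 15%. The section concludes: "The sample size calculation yielded a total of 92 participants to be randomized to two intervention groups".

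Study design and ethical approval gives 1:1 allocation. Randomization and blinding says "There will be 46 participants in each group", and the sections on the two treatment groups repeat 46. The Methods paragraph of the abstract also gives 92 patients, but has them "divided into two study groups (*n* = 40) to receive treatment", which sums to 80.

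The Sample size section mentions no multiplicity adjustment, baseline correlation or inflation factor other than the 15% loss. Data analysis also sets the significance level at 0.05.

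**The concern.** The article states every input to a standard two-group comparison of means and also states the result, so the result can be checked. It fails the check on three counts.

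- The difference, SD, alpha, power and loss rate do not lead to 92.
- Two measures of spread appear in one sentence. They differ, and nothing says how they relate.
- The abstract's group size does not match its own total or the body of the article.

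The RMDQ is the first-listed of three primary outcomes and the only one used for sizing. This paragraph is therefore the reader's sole basis for judging what the trial can detect. If 46 in total were the true requirement, the trial would recruit twice as many people as its stated justification supports. If another SD or another alpha was used, the paragraph misreports it.

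**Working it through.** **Inputs** (Sample size section; 1:1 allocation from Study design): difference δ = 2.5; SD σ = 2.5, or σ = √10 = 3.16 from the variance of 10; two-sided alpha 0.05 (z = 1.960); power 85% (z = 1.036); loss 15%.

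**Step 1. Try to reproduce 92.** The normal-approximation size per arm is n = 2 × (1.960 + 1.036)² × (σ/δ)². The t-test size uses the noncentral t distribution. Loss is allowed for by dividing by 0.85 and rounding up.

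| Spread used | Method | Per arm before loss | Per arm after loss | Total |
|---|---|---|---|---|
| SD 2.5 | normal | 17.96 → 18 | 18/0.85 = 21.2 → 22 | 44 |
| SD 2.5 | t-test | 18.97 → 19 | 19/0.85 = 22.4 → 23 | 46 |
| Variance 10 | normal | 28.7 → 29 | 29/0.85 = 34.1 → 35 | 70 |
| Variance 10 | t-test | 29.7 → 30 | 30/0.85 = 35.3 → 36 | 72 |

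Multiplying by 1.15 instead of dividing by 0.85 gives totals of 42 to 44 (SD 2.5) or 68 to 70 (variance 10). The stated figure is not reproduced under either spread.

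**Step 2. Compare the two spreads.** SD 2.5 means variance 2.5² = 6.25. Variance 10 means SD 3.16. They are not the same quantity.

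**Step 3. What 92 delivers.** 92 × 0.85 = 78.2, or about 39 evaluable per arm. By the two-sided t-test at 0.05:

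| | SD 2.5 | SD 3.16 |
|---|---|---|
| Power for 2.5 points, 39 per arm | 99.2% | 93.1% |
| Power for 2.5 points, 46 per arm (no loss) | 99.7% | 96.3% |
| Difference detectable with 85% power, 39 per arm | 0.687 × 2.5 = 1.7 points | 0.687 × 3.16 = 2.2 points |

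**Step 4. The abstract.** 2 × 40 = 80, not 92. Reading 40 as the evaluable number per arm gives 80 × 1.15 = 92. The correct allowance for 15% loss is 80/0.85 = 94.1, or 96 if each arm is rounded up (40/0.85 = 47.1 → 48). At alpha 0.05, 40 per arm is also not the requirement under either spread (19 or 30 by the t-test).

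**The case against.** Four arguments can be made for the plan.

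**The two spreads may be different quantities.** The variance of 10 sits in a parenthesis about the patient population, and the SD of 2.5 is what the test assumes. Data analysis defines the efficacy variable as a difference from baseline. A raw-score variance of 10 and a change-score SD of 2.5 agree if the correlation ρ between baseline and follow-up satisfies 2 × 10 × (1 − ρ) = 6.25, so ρ is about 0.69. This stands to the extent that the mismatch is unexplained rather than a proven contradiction. The article does not state this reading, and neither spread yields 92 in any case.

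**A multiplicity adjustment may have been used.** There are three primary outcomes. With variance 10 and alpha 0.05/3, the t-test needs 39.1 per arm, and 39.1/0.85 = 46.0. Rounding to 40 and multiplying by 1.15 also gives 46. This is worth asking the sponsor about, but the article states alpha 0.05 and mentions no adjustment. If this was the calculation, the reported alpha is wrong.

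**The power is more than adequate.** This stands. The 85% target is exceeded under both stated spreads. A reader might infer that the trial is underpowered, or that a null result could not be interpreted. The document does not support either: the 2.5-point target is stated, 95% confidence intervals are planned, and power for that target is about 93% or 99%.

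**The full protocol may contain more.** The point here is not an omission. The article states the inputs and the result, and they disagree.

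A reader might also infer that a total of 46 was mistaken for a per-arm figure, since 92 is twice 46. The factor is exactly two only for the t-test version (the normal approximation gives 44), so this remains a guess.

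**Conclusion.** Wrong as written. From the stated difference, SD, alpha, power and loss rate the total is 46 (44 by the normal approximation), and from the variance of 10 it is 70 to 72. The stated 92 follows from neither, and 85% is not the power of this design for 2.5 points. The abstract's 40 per group is inconsistent with 92 in total and with the 46 per arm given consistently in the body.

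On the stated inputs the error is towards too many participants. That conclusion depends on one of the two stated spreads being right. If the true SD were 5, which is an assumption found nowhere in the document, power for 2.5 points would be about 66% with 46 per arm and 59% with 39. This is why the SD needs a source. The calculations assume a two-sample comparison of means, 1:1 allocation and 15% loss in each arm.

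**What to change.** Keep 92 randomised (46 per arm) and correct the text:

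1. State one SD with its source, and say whether it applies to raw RMDQ scores or to change from baseline.
2. Remove the other measure of spread, or explain how it relates to the first.
3. State the alpha actually used, including any adjustment for the three primary outcomes.
4. Restate the power, or the detectable difference, at about 39 evaluable per arm. At alpha 0.05 this is 99% for 2.5 points, or 85% for 1.7 points, if the SD is 2.5; and 93% for 2.5 points, or 85% for 2.2 points, if the SD is 3.16.
5. Correct the abstract to 46 randomised per arm.

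Do not choose an SD because it makes 92 come out. A value of about 3.6 would do so at 39 per arm, but it has no source in the document. The cost is wording only, with no change to enrolment.

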### Data analysis

Statistical analysis will be performed using SPSS© version 21.0 and STATA 14 using the principles of intention to treat. Comparisons will be made between the two study arms. We will calculate the difference between the groups after the final treatment session and at 2 months post-intervention (short-term results).

The efficacy variable for this clinical trial is the difference between continuous variables (i.e., RMDQ, ODI, VAS, TSK, SF-36, PSQI, HADS, pressure algometry, McQuade test and trunk range of movement) at baseline and at predetermined time points (electric dry needling treatment vs conventional physiotherapy):

The Kolmogorov-Smirnov test will be used to assess the normality of continuous variables.

The equality of means of the intragroup hypotheses will be analysed using Student’s *t* test for paired clinical variables in the case of parametric distributions and the Kruskal-Wallis *H* test in the case of nonparametric distributions.

One-way analysis of variance (ANOVA) will be used to test the intragroup hypothesis in the case of parametric distributions, and the Kruskal-Wallis *H* test will be used in nonparametric distributions.

Post hoc analysis will be obtained for parametric distributions and Mann-Whitney *U* for nonparametric distributions.

The confidence interval will be set at 95% and the level of significance at 0.05.

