### Data collection

At the beginning of the study, the following demographic data will be collected: age, sex, weight, height, education and clinical presentation. Primary and secondary outcome measures will be evaluated at baseline prior to randomization to different groups. This will be followed by an immediate post-treatment assessment (1 day after the final intervention) and an evaluation 2 months after the end of the intervention (short-term follow-up).

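### Efficacy is set as change from baseline with covariate-free tests, although a pre-randomisation value exists for every outcome; a baseline-adjusted arm comparison would usually be more precise, by a modest amount

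*Protocol article*

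**What the plan says.** The Data analysis section defines the endpoint: "The efficacy variable for this clinical trial is the difference between continuous variables", listing RMDQ, ODI, VAS and the secondary scales, with values at baseline set against those at the planned time points in the two arms. It also says that the difference between groups will be calculated after the last session and at 2 months, without saying whether this is a difference in change or in follow-up scores.

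It then names the tests. The t test is paired and is assigned to intragroup hypotheses. For the ANOVA it says: "One-way analysis of variance (ANOVA) will be used to test the intragroup hypothesis in the case of parametric distributions". Kruskal-Wallis is the fallback when normality is rejected, with Mann-Whitney as its post hoc test. No ANCOVA, regression or mixed model appears anywhere in the article.

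On the availability of baseline values, the Data collection section says: "Primary and secondary outcome measures will be evaluated at baseline prior to randomization to different groups". Table 1 schedules all the clinical variables at the pre-treatment visit.

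**The concern.** When baseline and follow-up are imperfectly correlated, subtracting the whole baseline value generally takes off too much or too little. With similar SDs at both visits it takes off too much: patients who start high tend to fall further whatever the treatment. An arm that by chance starts higher then appears to improve more. The Randomization and blinding section describes a random-number table at 1:1 with 46 per arm and mentions no stratification, so a chance imbalance of ordinary size should be expected.

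What is at stake is precision, and how far the estimate depends on the luck of the draw. The wider interval and the shift with imbalance are largely one cost seen from two sides. The endpoint form and the tests are written down here, so this is not a detail left open for a statistical analysis plan.

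**Working it through.** **Inputs.** From the protocol article: 46 per arm and 15% loss, so about 46 × 0.85 ≈ 39 completers per arm (78 in all); a target difference of 2.5 RMDQ points; and two dispersion figures in the Sample size section, a variance of 10 (SD 3.16) and an SD of 2.5. Assumed: baseline/follow-up correlation ρ of 0.5 to 0.7, and a ratio k of follow-up SD to baseline SD of 1 or 1.25.

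**The plan's own figure.** The plan states no precision for the efficacy contrast, only a total of 92. With n per arm = 2(1.960 + 1.036)²·SD²/2.5², SD 2.5 gives 18 per arm (44 in all after dividing by 0.85 and rounding up per arm). Variance 10 gives 29 per arm (70 in all). Neither gives 92, and the section does not say whether its SD is of scores or of change. That is a separate matter, and the comparison below does not depend on it.

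**Variance per patient.** With baseline SD s₀ and follow-up SD s₁ = k·s₀:

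- change: s₀²(1 + k² − 2ρk)
- follow-up score alone: s₀²k²
- ANCOVA: s₀²k²(1 − ρ²)

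Change minus ANCOVA equals (s₀ − ρs₁)², which cannot be negative. At k = 1 the ratio of ANCOVA to change reduces to (1 + ρ)/2.

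| k | ρ | change / s₀² | ANCOVA / s₀² | ratio | variance saved |
|---|---|---|---|---|---|
| 1 | 0.5 | 1.000 | 0.750 | 0.75 | 25% |
| 1 | 0.7 | 0.600 | 0.510 | 0.85 | 15% |
| 1.25 | 0.5 | 1.3125 | 1.1719 | 0.89 | 11% |
| 1.25 | 0.7 | 0.8125 | 0.7969 | 0.98 | 2% |

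At k = 1 the standard error is √0.75 = 0.87 or √0.85 = 0.92 of the change-score one, so intervals are about 13% or 8% narrower. In terms of completers, 78 analysed by ANCOVA are worth 78/0.75 = 104 or 78/0.85 ≈ 92 analysed by change.

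A simulation with k = 1, 39 per arm and 10,000 runs agrees. Standard errors in SD units, change against ANCOVA, were 0.226 and 0.195 at ρ = 0.5, and 0.176 and 0.163 at ρ = 0.7.

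Estimating the slope costs about 1.4% of variance with 78 completers. At k = 1 ANCOVA stays ahead until ρ is about 0.97. At k = 1.25 and ρ = 0.7 this cost uses up most of the 2%.

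**If follow-up scores alone are compared.** ANCOVA saves ρ² of the variance: 25% at 0.5 and 49% at 0.7.

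**Effect of chance imbalance (k = 1).** Per point of baseline difference, the change-score estimate moves by −(1 − ρ): −0.5 or −0.3 point. The standard error of the baseline difference is √(2/46) = 0.21 SD, which is 0.66 RMDQ points at SD 3.16 or 0.52 at SD 2.5, if those SDs apply to baseline scores. A one-standard-error imbalance therefore moves the estimate by 0.33 or 0.20 points at SD 3.16 (ρ = 0.5, 0.7), and by 0.26 or 0.16 at SD 2.5. That is about 6% to 13% of the 2.5-point target. Under a linear model ANCOVA removes this shift.

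**The case against.** The strongest reply is that nothing here is invalid. Under randomisation a change score gives an unbiased arm contrast with correct type I error, so the plan loses efficiency and no more. That stands. The practical loss on RMDQ may also be small: if the SDs in the Sample size section are SDs of change, 39 completers per arm give about 93% (SD 3.16) to 99% (SD 2.5) power without adjustment. The gain rests on ρ and k, neither of which is given. At k = 1.5 and ρ = 0.7 it is essentially nil (1.1475/1.15 = 0.998). All of this limits the size of the point.

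It can also be said that the section names no clear parametric between-arm test, since its t test and ANOVA are both labelled intragroup. That is so, and it is a further reason to specify one. Whether the planned contrast is of change or of follow-up scores, it is unadjusted.

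A reader might infer that enrolling only patients with RMDQ of at least 4 adds regression to the mean and so distorts the contrast further. The documents do not support this. The criterion applies to both arms alike, so the fall it induces cancels in expectation. If the screening score also serves as baseline, selecting on it does not alter a linear slope of follow-up on baseline. The criterion also concerns RMDQ only.

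**Conclusion.** The point holds as a nearly free improvement, not as a fault of validity. The stated efficacy variable discards information that the trial already collects. For ρ of 0.5 to 0.7, adjusting for baseline cuts the variance of the arm contrast by about 25% to 15% with equal SDs, or by about 11% to 2% if the follow-up SD is 1.25 times the baseline SD. In large samples it is never worse than change. A one-standard-error imbalance in RMDQ would move the unadjusted estimate by roughly 0.2 to 0.3 points at equal SDs. These sizes are assumption-bound, but the direction is not, apart from the small cost of one estimated slope. A reader should not conclude that the planned analysis is biased or that its p-values would be wrong.

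**What to change.** Amend the Data analysis section so that the between-arm efficacy analysis of RMDQ and every other continuous outcome is an ANCOVA at each time point: follow-up value as response, arm and that outcome's baseline value as covariates, reported as an adjusted mean difference with 95% CI. A mixed model over both follow-up visits with baseline, arm, visit and arm-by-visit terms is an equivalent choice. For the arm comparison this replaces the ANOVA labelled intragroup and the normality-driven switch to rank tests. If skewness is a worry, a bootstrap interval can be given as a sensitivity analysis. Keep within-arm change as description only.

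The change needs no extra patients, visits or measurements, uses one degree of freedom, and runs in the SPSS and STATA packages already named. It is not quite cost-free. The Ethics and dissemination section says that analyses will not be modified after the first enrolment, while providing for amendments that are notified to the institutional committee and reported with the results. The change should go through that route before the data are analysed; made after the results are seen, it would have to be labelled post hoc.

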### Adverse effects

No potential risks have been described so far, given that these can be prevented by the operator’s knowledge of anatomy, training and experience [60]. Researchers will notify study participants of possible adverse events in the informed consent and record any adverse events that occur over the course of the study. If such events are observed, the frequency of occurrence will be analysed between the groups, and if patients have any questions or require additional information about any symptoms, they will be able to contact the physiotherapists by phone or email. Periodic reviews of security protocols will be carried out with staff.

### Ethics and dissemination

All participants will receive verbal and written information about the study before giving their consent to participate. They will be informed that they can leave the study at any time. Participants who agree to take part in the study will sign two copies of the informed consent form, one for the research and evaluation team and one for the participant.

All hard copies will be confidential and stored in a locked filing cabinet in the research group office and in electronic format in a password-protected database. The research team will monitor the integrity of the trial data. All participants, group assignments, treatment records and sociodemographic data will be coded, and the results of the questionnaires will be scored.

The data collected on each participant will be kept under lock and key by the evaluator. If the data are in digital format, they will be stored in a computer with a secret access code known only to the evaluator.

The eligibility criteria, results and analyses will not be modified once the first participant has been enrolled in the study. Any amendment to the protocol, including changes in the eligibility criteria, the results or the analyses, will be communicated to the Institutional Research Committee of the University of Almería and reported in articles and presentations disseminating the results of the trial.

The feasibility results will be published in peer-reviewed journals and presented at academic, clinical and health services conferences.

